#### Rationale for intervention

##### Establishment of PMU, PMC, PDK plus community orientation of doctors, ANMs and ASHA workers

Strengthening the capacity CHCs, PHCs and SCs for the management of CAP will result in better delivery of pneumonia specific care; this will build community’s trust in the public health system.

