##### Behavior change communication for demand generation for pneumonia management by the community

To ensure optimal utilization of augmented health facilities by measures mentioned above, a behavior change in the community will be needed, with respect to management of CAP. This behavior change can be brought about by various BCC strategies that utilize the messages developed by us. Effective behavior change is likely to result in demand generation for better quality of care from the public health sector for CAP by the community.

To identify the most effective BCC strategy, PAS will be conducted for caregivers who voluntarily bring their children for immunization either at the PHC/CHC or on VHND at the *anganwadi* center (AWC) as are likely to be receptive to health education messages. There will also be diffusion of messages in the community. PAS will bridge the gap and build confidence of the community in the public health system and services. We will be able to identify what is the minimum effective package of services that will result in optimal utilization of augmented public health facilities.

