#### Process

##### Pre-intervention phase (6 months)

Standard operating procedures, training modules and data collection tools will be developed. Supplies (including drugs) will be procured. Working closely with the government, PMC and PMU will be established in APHC and CHC, respectively. Health staff will be trained. Baseline line Survey will be conducted in intervention and control areas to assess the burden of Acute Respiratory Illness (ARI)/CAP in under-5 children, care seeking pattern and behavior, socio-demographic conditions of households, health infrastructure and skills of service providers (KAP) for management of ARI/CAP. Survey will be carried out using population proportion sampling using 30 cluster methodology [10]. In all 2400 households will be selected from 240 villages.

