*Intervention 2:* PAS will be conducted during V.H.N.D. monthly by the ASHA worker for caregivers who congregate there using (a) case-stories (text formats) (b) messages for early recognition of pneumonia, when and where to seek care, risk perception of delayed treatment or treatment from unqualified provider and also recognition of danger signs of pneumonia through the self-developed posters, as well as (c) inform the community about infrastructural strengthening, PDK, PMC, PMU and (d) respond to queries.

*Intervention 3:* Combination of Both Intervention 1 & 2:

*Intervention 4:* This will be the Usual Care arm. In this arm only PDK, PMC and PMU will be established. No IEC will be done in the villages or APHC/CHC. Children in in the usual arm group will receive the same standard care and services provided to all children and their families residing in the area.

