Univariate distribution of baseline and outcome variables would be assessed by frequency counts. Outliers will be identified, reported and excluded from analysis if required. They would be compared between interventions using chi square test for categorical and Student’s t test and ANOVA for continuous variables. A *p* value of < 0.05 will be taken as statistically significant, using a two tailed distribution. Adherence to the intervention across each arm will be calculated and compared across the three arms (as one was a control arm). Good intervention is defined as > 75% adherence to the sessions in the duration of the project. Primary outcomes will be number of PDK kits distributed to children plus the number of children treated by government functionaries for acute respiratory infection (ARI) or pneumonia without PDK, using medicines available at the health facility in interventions given by ANMs/ASHA workers. If we find that the diagnosis of children being treated is not mentioned, then we fill this missing information by extrapolation from data where diagnosis is given for the same month and within the intervention arm, assuming that there would be similar proportion of cases with this diagnosis. We will compute the difference in the proportion of ARI/pneumonia treated in each intervention arm when compared to control arm in the intention to treat analysis. For the secondary outcome, we will compare the proportion of cases with ARI/pneumonia treated by government providers as their first choice in interventions given by ANMs/ASHA workers, as an intention to treat analysis. In the per-protocol analysis we will compare the proportion of cases with ARI/pneumonia treated by government providers as their first choice in interventions given by ANMs/ASHAs from those households which have participated in the baseline as well end line survey using paired t-test. As a sub-analysis, we will compare the mean, median and interquartile range of out of pocket expenditure for ARI/pneumonia in the baseline and end line survey within each arm. As a comparator, we will do similar analysis for cases who have suffered from diarrhea to assess whether changes in spending were a function of time or because of care seeking from government providers, which is most inexpensive.

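### Separate before-after comparisons of ARI and diarrhoea spending cannot tell a time trend from an effect of government care seeking, and diarrhoea may not be a clean marker of time

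*Protocol article*

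**What the plan says.** Under Data management & analysis plan, the protocol article describes a sub-analysis of household spending that will "compare the mean, median and interquartile range of out of pocket expenditure for ARI/pneumonia in the baseline and end line survey within each arm". Diarrhoea is then brought in as comparator, through a "similar analysis for cases who have suffered from diarrhea to assess whether changes in spending were a function of time or because of care seeking". The second explanation is completed as "care seeking from government providers, which is most inexpensive".

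No contrast between the ARI change and the diarrhoea change is stated, and no test is named for spending. The same section sets a general rule that a p "value of < 0.05 will be taken as statistically significant, using a two tailed distribution".

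Three other places bear on whether diarrhoea care would stay unaffected:

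- The rationale for strengthening facilities says it "will build community’s trust in the public health system".
- The rationale for the awareness sessions says "PAS will bridge the gap and build confidence of the community in the public health system and services".
- The description of the usual care arm says "In this arm only PDK, PMC and PMU will be established", so the strengthening package reaches every arm.

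On survey size, the Pre-intervention phase section says "In all 2400 households will be selected from 240 villages". The article does not give the number of ARI or diarrhoea cases with spending data.

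**The concern.** The question has two competing answers: spending on ARI changed because time passed, or because families moved to cheaper government providers. To choose between them one must know whether ARI spending changed more than diarrhoea spending. Two separate before-after comparisons do not address that. Each asks only whether spending on its own illness changed.

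This can mislead in two directions.

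1. **Time read as care seeking.** Both illnesses follow the same trend, but the change is clear for ARI and unclear for diarrhoea, for example because there are fewer diarrhoea cases.
2. **Care seeking read as time.** The project raises confidence in government services generally, diarrhoea cases move to government providers too, and diarrhoea spending falls alongside ARI spending.

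At stake is the statement on household savings. A price trend could be reported as a benefit, or a real saving dismissed as trend.

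**Working it through.** The document gives no power or error rate for this analysis, so there is no figure to reproduce. The check shows how the scheme behaves under stated assumptions.

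**From the document.** 2400 households in 240 villages is 10 per village. Over four arms, split equally, that is 600 households and 60 villages per arm. The general alpha is 0.05, two-sided.

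**Assumed.** Per arm and survey, 200 ARI cases and 60, 100 or 200 diarrhoea cases; SD of log spending 1.0; design effect (deff) 1.0 or 1.5; the two illnesses and the two surveys independent. The reading rule is also assumed: ARI significant and diarrhoea not means care seeking; both significant means time.

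**Formulas.** For one illness, SE = SD × √(2 × deff / n). A fall of f is a shift d = −ln(1 − f). Power = Φ(d/SE − 1.96) + Φ(−d/SE − 1.96). For the ARI-minus-diarrhoea contrast, SE = √(SE_ARI² + SE_D²).

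**Direction 1: the same fall in both illnesses, time only.** Worked example with 200 ARI and 60 diarrhoea cases, deff 1.0, fall 20%: d = 0.223, SE_ARI = √(2/200) = 0.100, SE_D = √(2/60) = 0.183. Power is 0.607 for ARI and 0.231 for diarrhoea. Chance of crediting care seeking = 0.607 × (1 − 0.231) = 0.467.

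| ARI / diarrhoea cases, deff | fall 10% | 20% | 30% | 40% |
|---|---|---|---|---|
| 200 / 200, 1.0 | 0.150 | 0.239 | 0.051 | 0.001 |
| 200 / 100, 1.0 | 0.162 | 0.394 | 0.272 | 0.049 |
| 200 / 60, 1.0 | 0.167 | 0.467 | 0.475 | 0.201 |
| 200 / 60, 1.5 | 0.128 | 0.370 | 0.533 | 0.368 |

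A direct contrast of the two changes has a false-positive rate of 0.050 in every cell, provided the proportional trend really is equal in both illnesses.

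**Without any p-value.** Suppose the two changes are only judged side by side. With 200 and 60 cases and deff 1.0, the SE of their difference is √(0.100² + 0.183²) = 0.208, and 1.96 × 0.208 = 0.408 on the log scale. Under an identical trend, the two observed ratios of change can differ by a factor of up to e^0.408 = 1.50 within ordinary 95% chance limits. With 100 diarrhoea cases, SE_D is √(2/100) = 0.141, the SE of the difference is 0.173 and the factor is 1.40. The unaided eye has no guide to this; an interval on the contrast supplies it.

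**Direction 2: ARI spending falls 40% wholly through care seeking.** The ARI shift is 0.511, and diarrhoea takes a share s of it. Worked example with 200/100, deff 1.0, s = 0.5: the diarrhoea shift is 0.255, so its power is Φ(0.255/0.141 − 1.96) = 0.439. ARI power is 0.999, so both are significant, and the change is read as time, with probability 0.439.

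| Share s reaching diarrhoea | Read as time, 200/100, deff 1.0 | Read as time, 200/60, deff 1.5 | Power of contrast, 200/100, deff 1.0 | Power of contrast, 200/60, deff 1.5 |
|---|---|---|---|---|
| 0 | 0.050 | 0.049 | 0.839 | 0.517 |
| 0.5 | 0.439 | 0.205 | 0.314 | 0.171 |
| 0.75 | 0.772 | 0.397 | 0.114 | 0.079 |
| 1 | 0.950 | 0.619 | 0.050 | 0.050 |

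The contrast repairs direction 1 but not direction 2: as spillover grows, the difference it measures disappears.

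**The case against.** The strongest objection is that the article states no decision rule for spending. It says the summaries will be compared, and the p < 0.05 sentence follows the description of comparisons between interventions. Setting two changes side by side is what a comparator is for. This is also a sub-analysis in a condensed article, where the exact test may be left to a fuller plan. What stands: a reader might infer that the protocol commits to testing each illness for zero change and reading off significance, and the text does not support that. The p-value rule above is an inference, and its percentages do not describe a rule the trial has adopted. The weakness does not depend on it, since judging two changes by eye has the same gap.

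Second, session content is largely specific to pneumonia, as are the drug kit and the earmarked beds, so another childhood illness is a reasonable comparator. This stands in part. A reader might infer that diarrhoea spending will move with the intervention, and the document does not show that. But it does not argue the opposite either, and both rationale passages aim at trust in the public system as a whole. The usual care arm does not resolve the doubt, because it also receives the kit, the corners and the units.

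Third, one might answer the question from the ARI data alone, by splitting the change into a shift between providers and a change within provider type, and calling the second part time. The objection to that is sound. Kits supplied by the project can lower spending within government care, and choice of provider is related to severity. Labelling the within-provider part as time would repeat the fault.

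**Conclusion.** The point holds in a limited form. Separate within-arm comparisons do not answer the question the protocol sets, and diarrhoea spending is not a secure marker of time. Either error is possible.

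Under the stated assumptions and the inferred p-value reading, a common trend is credited to care seeking in 0.1% to 53% of trials. The low end needs equal case counts and a large trend; the high end needs few diarrhoea cases. A real 40% fall is read as time in about 21% to 95% of trials when half or more of the effect reaches diarrhoea, and in about 5% when none does. These ranges rest on assumed case counts, SD, design effect and spillover, none of which the document gives, so they show sensitivity and do not predict this trial's error rate.

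A reader might infer that the trial's main findings are at risk. They are not: spending is a sub-analysis, and the primary and secondary outcomes do not depend on it. The change is worth making because it is cheap and the spending statement could otherwise be wrong in either direction.

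**What to change.** For this sub-analysis:

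1. Replace the two separate comparisons with one illness-by-survey contrast per arm, the ARI/pneumonia change minus the diarrhoea change, with a 95% confidence interval that respects clustering by village. The descriptive means, medians and interquartile ranges can stay.
2. Report it beside the baseline-to-end-line change in the share of diarrhoea cases treated by government providers, where recorded, as a check on spillover.
3. State that a parallel fall in diarrhoea spending does not prove a time trend.
4. If ARI spending change is also split by provider type, label it descriptive and do not call the within-provider change the time component.

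The cost is a few sentences of analysis text and a little programming. No new ARI data are needed; the spillover check needs the provider for diarrhoea cases. The downside is that the contrast is less precise than either single comparison (SE 0.173 against 0.100 and 0.141 with 200/100 cases and deff 1.0) and has little power if spillover is large. Item 2 is there to make that visible.

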#### Process indicators

Capacity building of health staff through trainings at the initiation of process and retraining after one year. Proportion of doctors, ANMs and ASHAs trained by each intervention block will be computed.Establishment of PMC and PMC: For this we will request the government to pass relevant orders. Project and government will provide materials as given in Table 3.Distribution of PDK: Project will purchase and repackage the medicines and distribute them at various health facilities. From here PKD will be given to the ANMs also. This will be monitored by the project.Utilization of PDK: Project will monitor the number of PKDs distributed at each quarter in each block.Utilization of PMC and PMU: This will be assessed by number of cases of CAP admitted at each facility by intervention type.Conduct of BCC interventions: This will be verified by project staff continuously throughout the project. Quality assessment of the PAS sessions will also be done by taking feedback from a convenience sample of attendees.

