#### Trainings

##### Orientation of doctors, ANMs and on ASHA workers on prevalent community pneumonia management practices

The participants will be given the innovative `community orientation` to CAP using vignettes of real life cases of CAP, informed about community barriers to case management and their perceptions of health facilities. Thereafter, they will be shown the messages developed and told about the rationale behind each. They will be told about infrastructural strengthening, namely, PDK, PMC, PMU (Table 3). Additional training will be given to the care providers separately as given below.

**Table 3 Tab3:** Framework for Infrastructural Strengthening

Site	Infrastructural strengthening and purpose
Subcentre/PHC/CHC	PDK containing dispersible pediatric amoxicillin tablets (250 mg) PLUS instruction card will be provided by the project. Ten doses of amoxicillin (for a maximum of 5 days) will be kept in transparent envelop with *green sticker* for children below between 1 and 12 months and * yellow sticker* for children between 12 and 59 months. Each envelope will also have 4 tablets of paracetemol (500 mg). Within each envelope will have a small card with instructions for use of medicines on one side, and how to monitor a child with clinical pneumonia for improvement and deterioration on the other side will be kept. Instructions will be in Hindi.
APHC	PMC to treat pneumonia with fast breathing and stabilize &refer pneumonia with lower chest in-drawing with hypoxia (pulse-oximetry< 92%) and severe pneumonia. Project to provide: PDK, Pulse oximeter, spacer with baby mask, salbutamol inhaler. State Government Supply: Earmark ONE existing bed as *pediatric pneumonia bed,* storage facility for drugs, equipment and patient records and common facilities like 24X7 doctor-nurse; Injectibles: ampicillin, gentamycin, ceftrioxone, corticosteroid; Oral: antipyretics, co-trimoxazole; oxygen, face mask, suction machine and mucus extractors, laryngoscope, endotracheal-tube, ambu-bag, thermometer, pediatric blood pressure instrument.

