CHC	PMU to treat pneumonia with fast breathing and lower chest in-drawing and admit pneumonia with hypoxia (pulse-oximetry< 92%) and severe pneumonia. Project to provide: PDK, Pulse oximeter, spacer with baby mask, salbutamol inhaler. State Government Supply: Earmark TWO existing beds as *pediatric pneumonia beds,* storage facility for drugs, equipment and patient records and common facilities like 24X7 doctor-nurse; Injectibles: ampicillin, gentamycin, ceftrioxone, corticosteroid and vasopressors (dopamine), calcium, potassium, intravenous fluids like dextrose saline, Ringer Lactate; oral: antipyretics, co-trimoxazole; bronchodilators; oxygen, face mask,suction machine and mucus extractors, laryngoscope, endotracheal-tube, ambu-bag, thermometer, pediatric blood pressure instrument, nebulizer with nebulizer solutions of salbutamol, epinephrine and steroid, intravenous cannula, venous cut-open set, heater/warm air blowers for winter months.

*Abbreviations APHC* Additional Primary Health Centre, *PHC* Primary Health Centre, *CHC* Community Health Center, *PDK* Pneumonia Drug Kit, *PMC* Pneumonia Management Corner, *PMU* Pneumonia Management Unit

A brief refresher course on ARI module of F-IMNCI will be organized for doctors. Medical management of CAP in paediatric ward of a tertiary care teaching hospital will be demonstrated. Doctors will also be trained to record clinical data of CAP patients in simple to use case sheet prepared for the project. Training will be done in KGMU by F-IMNCI trained faculty.

A brief refresher course on ARI module will be also be organized for the ANMs in their respective CHCs. Investigators and faculty trained in F-IMNCI will impart training. ANMs will be trained to use drugs from PDK in the villages and SC and document it. They will also be trained to refer CAP with lower chest in-drawing or severe pneumonia by calling ambulance services by dialing 102/108. ANMs will be trained to conduct PAS using (a) case-stories (in video/text formats) (b) messages for early recognition of pneumonia, when and where to seek care, risk perception of delayed treatment or treatment from unqualified provider and also for recognition of the danger signs of pneumonia through the self-developed posters, audio and video messages as well as (c) inform the community about infrastructural strengthening, PDK, PMC, PMU and (d) respond to queries.

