##### Quarterly health facility audit

This will be done to collect data on process Indicators and will be used for the establishment of Management information-system. Process indicators will be (i) utilization of PDK, PMC and (ii) conduct of PAS sessions in APHC, CHC and during VHND as well as numbers attending it. This will be done by the project staff. Data will be abstracted from records of PHC/CHC and SC for number of clinical pneumonia treated either as outpatients or inpatients or referred (with reasons and place) in last 1 month, and utilization of PDK and availability of medicines and equipment for the treatment of CAP (both provided through the project and supplied from the government). This information will be collated and shared with the Medical officer-In Charge of the health facility, Chief Medical Officer of Lucknow and office of Mission Director, National Health Mission.

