A qualitative narrative of the process of establishment of the project will be given. Key informant and semi-structured interviews will be used to assess the level of satisfaction of stakeholders with (a) the services provided by public health facility augmentations and (b) IEC campaign strategies. Qualitative analysis techniques will be used for this data analysis.

Primary outcomes will be (a) number of patients of CAP treated by ANMs/doctors with medicines from PDK OR treated PMC OR PMU and (b) health service providers’ preference for treatment of CAP/ARI. For health facility utilization, the data will be abstracted periodically from the records maintained there. Feedback will be given to each facility on the process indicators within a month. For health provider preference, data from base line and end-line multistage cluster surveys will be used. At the end of the project the primary outcome measures will be compared in interventions given by ANMs/ASHA workers, using tests of proportion.

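### The process indicator for use of the pneumonia corners and units counts only admitted cases, which does not fit their roles in Table 3 and is narrower than the facility audit

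*Protocol article*

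**What the plan says.** The list under Process indicators defines use of the two facility types in one sentence: "Utilization of PMC and PMU: This will be assessed by number of cases of CAP admitted at each facility by intervention type".

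Table 3 (Framework for Infrastructural Strengthening) sets out what each facility is for. At the additional primary health centre (APHC): "PMC to treat pneumonia with fast breathing and stabilize &refer pneumonia with lower chest in-drawing with hypoxia (pulse-oximetry< 92%) and severe pneumonia". At the community health centre (CHC): "PMU to treat pneumonia with fast breathing and lower chest in-drawing and admit pneumonia with hypoxia (pulse-oximetry< 92%) and severe pneumonia". The APHC entry also says "Earmark ONE existing bed as" a paediatric pneumonia bed; the CHC entry earmarks two.

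The section Quarterly health facility audit names PMC utilization as a process indicator, with no restriction to admissions, and lists the data to be abstracted from facility records: "number of clinical pneumonia treated either as outpatients or inpatients or referred (with reasons and place").

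The Data management & analysis plan defines primary outcome (a) as "number of patients of CAP treated by ANMs/doctors with medicines from PDK OR treated PMC OR PMU".

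**The concern.** Utilization should measure how many children with CAP a facility manages. The stated measure counts one disposition only. For the PMC it is a disposition that Table 3 assigns to no group of children, so an APHC could manage many children exactly as planned and have little of that work appear in its indicator. An APHC that kept children whom Table 3 has it refer would score higher.

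The indicator is also to be reported by intervention type. The project aims at earlier recognition and care seeking. If earlier presentation changed the share of children who need admission, admissions and true use could move by different amounts, or in different directions.

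The protocol says that process indicators are fed back to each facility within a month, that audit information goes to the district and state health authorities, and that the PMC and PMU are to be scaled up across the state. A utilization figure that does not reflect the assigned work could mislead those readers.

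**Working it through.** The protocol gives no utilization figure to reproduce. The check sets the texts side by side and adds simple arithmetic.

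**1. Roles against the indicator (Table 3 and Process indicators)**

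| Group named in Table 3 | PMC (APHC) | PMU (CHC) | Counted as admitted? |
|---|---|---|---|
| Fast breathing | treat | treat | no |
| Lower chest in-drawing | named only with hypoxia: stabilise and refer | treat | no |
| Hypoxia or severe pneumonia | stabilise and refer | admit | PMU only |

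Read literally, no group named for the PMC leads to an admission there, so the role-based count is 0 for the corners. One of the PMU's assigned tasks is counted and the other is not.

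**2. Scope of the same concept elsewhere**

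- Process indicators: admitted cases only.
- Quarterly audit: outpatients, inpatients and referrals.
- Primary outcome (a): patients treated.

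The audit therefore already collects the groups that the indicator leaves out.

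**3. Scale of the ambulatory work**

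The section Medicines makes oral amoxicillin in the Pneumonia Drug Kit (PDK) the ambulatory treatment. It plans 10 kits a month per primary health centre (read here as per APHC) and 25 per CHC. With the facility numbers in Table 1:

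- APHCs: 28 × 10 = 280 kits a month, or 280 × 12 = 3,360 over the 12-month intervention phase.
- CHCs: 9 × 25 = 225 kits a month, or 225 × 12 = 2,700 over 12 months.

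These are supply figures, not case counts. They show only that the plan provides for ambulatory treatment at both levels, none of which is an admission.

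**4. Share missed at the PMU**

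If a share s of the CAP cases seen at a PMU is admitted, the indicator misses 1 − s. The documents give no s. Assumed range: s = 5% gives 95% missed; s = 30% gives 70% missed.

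**5. Is zero realistic at the PMC?**

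Not necessarily. There are 28 × 1 = 28 earmarked PMC beds (and 9 × 2 = 18 PMU beds). With an assumed stay of 3 to 5 days, the PMC beds could take 28 × 30/5 = 168 to 28 × 30/3 = 280 admissions per 30 days. Some admissions may therefore be recorded.

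**6. Direction between arms**

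Admissions A = N × s, with N the children managed. Hence A1/A0 = (N1/N0) × (s1/s0). Take an assumed control arm with N0 = 100 and s0 = 20% (A0 = 20), and an intervention arm with N1 = 130, so that true use is up 30%:

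- s1 = 20%: A1 = 26, up 30%. The indicator tracks true use.
- s1 = 20/130 = 15.4%: A1 = 20, no change.
- s1 = 15/130 = 11.5%: A1 = 15, down 25%.
- s1 = 25%: A1 = 32.5, up 62.5%.

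The indicator tracks true use only if the admitted share is the same in both arms. It falls while use rises by 30% only if s1/s0 is below 1/1.3 = 0.77. Nothing in the documents says which case applies.

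**The case against.** The strongest reply is that this is one line in a set of process indicators and not an outcome. The preceding item in the same list tracks PDK use. Since the PDK is the ambulatory treatment, many children with fast breathing seen at a PMC or PMU would appear there, and admissions would show use of the earmarked beds. The audit records referrals. A narrow indicator drawn from broader data is also not in itself a contradiction.

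Part of this stands. The audit does collect the missing groups, so information is not lost. But the PDK item counts kits per block and quarter, not cases per PMC or PMU, and it does not capture a child who was stabilised and referred without a kit. It cannot stand in for a measure of how far these facilities are used.

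Three stronger readings are tempting, and the documents do not support them:

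- A reader might infer that the primary outcome is compromised. Every definition of it, under Study aim and in the Data management & analysis plan, counts children treated or kits distributed. Nothing says that the admissions count feeds it.
- A reader might infer that most children are managed without admission and that a well-run corner scores near zero. Table 3 gives roles, not proportions. The earmarked bed, and the protocol's statement under Medicines that injectables for severe pneumonia are available at APHC level, leave room for some admissions. The PMU admits by design.
- A reader might infer that the indicator will point the wrong way. That needs a fall in the admitted share large enough to outweigh the rise in use. It is possible, not shown.

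**Conclusion.** The concern holds as an inconsistency within the protocol. The admissions-only definition does not fit the roles in Table 3 and is narrower than the audit that would supply the data. As written, it undercounts use of the PMC in particular (28 APHCs) and captures only the hypoxic or severe part of the PMU's work.

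The size is not known, because the documents give no case mix. The 70% to 95% missed at the PMU rests on an assumed admitted share of 5% to 30%, and the comparison between arms in the working is an assumed case mix. If the admitted share differs between arms, the indicator can overstate, understate or reverse the difference in use. If the share is the same, it tracks relative use correctly.

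The effect is confined to a process indicator and its use in feedback and reporting. The primary comparison is not defined by admissions and is not affected by this sentence.

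**What to change.** Reconcile the sentence under Process indicators with Table 3 and with the quarterly audit. For each PMC and PMU, and by arm, report three separate counts of CAP cases: treated as outpatients, stabilised and referred, and admitted. Take them from the existing audit fields, and state the period they cover, since the audit abstracts the last month. Show admissions as one component, not as the sole measure of utilization.

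Do not add the combined count to the primary outcome. A child referred from an APHC to a CHC, or an outpatient given a PDK, could be counted twice, and the protocol says that identifiers will not be noted in the data collection instruments, so duplicates could be hard to remove.

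The cost is a revised sentence and slightly more tabulation, with no new data collection. No clinical rule changes.
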